### Study Objective

The primary objective of this study is to report feasibility in accordance with the methodology described by Lancaster and Dodds [5], specifically addressing:

1) baseline survival rates for the treatment and control group to aid in the design of a definitive multicentre trial;

2) randomization compliance rate;

3) ease of protocol implementation in the out-of-hospital setting;

4) adverse event rate of HSD infusion.

The secondary objectives include measuring the effect of HSD in modulating the immuno-inflammatory response to severe head injury and its effect on modulating the release of neuro-biomarkers into serum; evaluating the role of serum neuro-biomarkers in predicting patient outcome and clinical response to HSD intervention; and evaluating effects of HSD on brain atrophy post-injury and neurocognitive and neuropsychological outcomes.

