### Safety and Dependability

The Paramedic Data Checklist (Additional File 10) and both the land and air prehospital (Additional File 11&12) and inhospital (Additional File 13) Case Report Forms explicitly ask whether or not adverse drug reactions with a definite causal relationship to the HSD have occurred. These adverse drug reactions will be predetermined by the Steering Committee based on the literature where possible. (Table 1) The Steering Committee will validate all outcomes and determined adverse events blinded to treatment assignment. This feasibility trial is approved by the Institutional Research Ethics Board.

**Table 1 T1:** Adverse Event Definitions

Event	Expected	Unexpected
**Brain Injury** **(Serious)**	**Demyelination** Any text reference in imaging reports to 'Central Pontine Myelinosis or Pontine Hyperintensity' in any MRI report during hospital stay	**Subarachnoid Hemmorhage** Any text reference in imaging reports of CT of MRI within 24 hours of arrival to Emergency Department to 'Subarachnoid Hemmorhage or SAH' when the first CT scan was normal

**Anaphylactoid Reaction** **(Serious)**	Any text reference in physician notes within the first 24 hours of arrival to Emergency Department to 'anaphylactoid reaction'	

**Prolonged Partial Thromboplastin Time** **(Non serious)**	Normal up to 40 May see up to 85 with HSD	> 100

**International Normalized Ratio** **(Non serious)**	Normal up to 1.5 May see up to 3.0 with HSD	> 3.0

**Serum Sodium** **(Non serious)**	Normal range 135-147 May see up to 158 with HSD	> 160

**Serum Osmolarity** **(Non serious)**	Normal range 310-330 May see up to 350 with HSD without alcohol	> 350 without alcohols

**Serum Chloride** **(Non serious)**	Normal range 96-108 May see up to 145	>150

**Rouleau formation** **(Non serious)**	May be present	

MRI Magnetic Resonance Imaging

CT Computerized Tomography Scan

SAH Subarachnoid Hemmorhage

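### Table 1 counts a new subarachnoid haemorrhage after a normal first CT as an adverse event, but no other type of new intracranial bleed under the same conditions

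*Protocol article*

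**What the plan says.** Study Objective in the protocol article lists four primary feasibility items. The fourth is the "adverse event rate of HSD infusion".

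Safety and Dependability describes how events are found. The paramedic checklist and the case report forms "explicitly ask whether or not adverse drug reactions with a definite causal relationship to the HSD have occurred". On which reactions these are, it says: "These adverse drug reactions will be predetermined by the Steering Committee based on the literature where possible", and it then cites Table 1, Adverse Event Definitions. On validation it says: "The Steering Committee will validate all outcomes and determined adverse events blinded to treatment assignment".

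The Brain Injury row of Table 1, classed as serious, has two entries:
- Expected: demyelination, found by a text search for two pontine terms "in any MRI report during hospital stay".
- Unexpected: subarachnoid haemorrhage, found by a text search of CT or MRI reports "within 24 hours of arrival to Emergency Department to 'Subarachnoid Hemmorhage or SAH' when the first CT scan was normal".

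Two laboratory rows, both classed as non-serious, concern clotting. For partial thromboplastin time the table gives "Normal up to 40 May see up to 85 with HSD", and for INR "Normal up to 1.5 May see up to 3.0 with HSD".

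**The concern.** The subarachnoid entry has a clear logic. A scan without blood followed by a scan with blood, soon after the infusion, identifies a bleed that was not visible at baseline. That logic does not depend on where in the skull the new blood lies. The entry nevertheless applies it to one location only.

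At stake is what the fourth feasibility endpoint counts. If the rate is built from the Table 1 definitions, two patients with the same course (normal first CT, new intracranial blood on a second scan at, say, 12 hours) are treated differently. The one with subarachnoid blood has a serious unexpected event, and the one with a subdural or intracerebral bleed has no Table 1 event. The endpoint is meant to inform a definitive trial, and the Discussion offers the data capture forms to later trials, so a narrow definition could be carried forward.

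**Working it through.** No formula or sample size figure is involved. The check is to read each row of Table 1 and ask whether it would catch a new subdural, extradural or intracerebral bleed seen within 24 hours of ED arrival after a normal first CT.

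1. Brain Injury, expected column: demyelination terms only. No.
2. Brain Injury, unexpected column: subarachnoid haemorrhage or its abbreviation only. No.
3. Anaphylactoid reaction: a phrase in physician notes. No.
4. Prolonged partial thromboplastin time: a laboratory value. No.
5. INR: a laboratory value. No.
6. Serum sodium, osmolarity and chloride (three rows): laboratory values. No.
7. Rouleau formation: a laboratory finding. No.

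Result: of eight rows, one contains a bleed, and no row catches the other three types.

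Next, does anything elsewhere in the article close the gap?
- Data Management has head CTs read by the Marshall classification. This is in-hospital patient data, not an adverse event definition.
- Structural Outcomes lists haemosiderin on gradient echo MRI. Intervention Protocol plans the MRI for 4 months, in consenting patients. This too is tied to no safety definition.
- Survival at 48 hours, discharge and 30 days would reflect a fatal bleed but would not identify it as a bleed.

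Finally, can the restriction to one bleed type be explained from the text?
- Attribution: the forms ask about definite causation by HSD. Requiring a normal first CT serves that aim, and it is a coherent reason to leave out growth of existing bleeds. It serves the aim equally well for subdural, extradural and intracerebral bleeds. Trauma can also cause subarachnoid bleeding, so background injury does not set that type apart.
- Expectedness: subarachnoid haemorrhage stands in the unexpected column, so the table is not confined to known effects of HSD.
- Literature: the article says the list draws on the literature where possible, but gives no reason for this one choice.

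**The case against.** The strongest reply is that the article does not say Table 1 is exhaustive. The case report forms are in Additional Files that are not shown, in-hospital staff abstract charts daily, and the Steering Committee validates outcomes and adverse events. The list rests partly on literature that cannot be seen here, and a condensed article need not justify each entry. This stands in part: new bleeds of other types may well be recorded and reviewed. But the article prints the definitions itself, with search terms and windows, and refers to them as the predetermined reactions. A bleed recorded elsewhere would still lie outside them.

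Three stronger readings are tempting, and the documents do not support them.

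- A reader might infer that the plan contradicts itself by expecting impaired clotting while not looking for bleeding. The table does allow partial thromboplastin time to reach about 2.1 times the upper normal limit (85/40 = 2.125) and INR 2.0 times (3.0/1.5). These are limits of what may be seen. The step from longer clotting times to bleeding is a clinical inference that the article does not make, and it lists subarachnoid haemorrhage under brain injury, apart from the clotting rows.
- A reader might infer that the window should be 48 hours, since coagulation is sampled at arrival, 12, 24 and 48 hours. That is a biomarker schedule. The article does not say how long any clotting effect lasts, and 24 hours is also the window for anaphylactoid reactions. Nothing shows that 24 hours is wrong.
- A reader might infer that the rate is diluted by patients discharged early and never rescanned. The article states no denominator for the rate, and denominators are ordinary analysis plan content. That such patients have normal scans and no second scan is a guess.

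**Conclusion.** The point holds in a limited form. Table 1 defines one type of new intracranial bleed as an adverse event and leaves out three others that meet the same conditions and would be found in the same reports. The article gives no reason for the difference.

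The size cannot be stated. It depends on the bleeding rate, the share of patients with a normal first CT and the share of those rescanned within 24 hours, none of which is given. With a planned recruitment of 100 and no repeat CT described, the number of affected patients could be small.

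The conclusion assumes that the endpoint rate is built from the Table 1 events, which the reference to the table suggests but the article does not spell out. It would be too strong to say that such bleeds go unrecorded, or that the trial's safety data as a whole cannot speak to bleeding, because the forms are not shown. This is a weakness in one definition and can be mended by rewording.

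**What to change.** Reword the unexpected entry of the Brain Injury row as: new intracranial haemorrhage of any type (subarachnoid, subdural, extradural, intracerebral) on a CT or MRI report within 24 hours of ED arrival when the first CT was normal. Abstract it from the same imaging reports, and have the same blinded Steering Committee validate it.

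The cost is three more bleed types in a text search already planned, with no new scans. The downside is a few more recorded events in both arms. Some will be due to the trauma itself, so the count has to be read against control. Bleeds in patients who are not rescanned will still be missed.

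Two additions are optional. The window could be extended to 48 hours, which is practicable because the same row already searches MRI reports over the whole hospital stay for demyelination. The report could also give, by arm, the number with a normal first CT and the number of those rescanned within the window, to show in how many patients such an event could have been seen.

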## Methods/Design

### Study design

The Toronto Prehospital Hypertonic Resuscitation-Head Injury and Multi Organ Dysfunction Trial (TOPHR HIT) is a randomized, placebo-controlled trial of blunt trauma patients with head injuries. The study compares a group receiving normal saline according to a paramedic's protocol, with a treatment group receiving a single dose 250 ml of 7.5% hypertonic saline in 6% dextran 70 (RescueFlow^® ^BioPhausia AB, Stockholm Sweden). The study was approved by the Canadian Therapeutic Products Directorate Control Number 092523 and registered at http://www.clinical.trials.gov. Inclusion and exclusion criteria are summarized in Additional file 1.

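### Table 1's osmolarity row and upper chloride limits are inconsistent with its sodium row, so normal osmolarity readings and low unexpected counts in those two rows would not show HSD to be safe

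*Protocol article*

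**What the plan says.** The fourth primary feasibility item under Study Objective is the "adverse event rate of HSD infusion". Safety and Dependability says that the reactions to be counted are fixed in advance by the Steering Committee, from the literature where possible, and refers to Table 1 for the definitions. The Committee judges events without knowledge of treatment assignment.

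Three rows of Table 1 follow the direct effect of the salt load. All three are labelled non serious, and none prints units.

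- Sodium: "Normal range 135-147 May see up to 158 with HSD"; unexpected above 160.
- Osmolarity: "Normal range 310-330 May see up to 350 with HSD without alcohol"; unexpected "> 350 without alcohols".
- Chloride: "Normal range 96-108 May see up to 145"; unexpected above 150.

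Under Study design, the product is a "single dose 250 ml of 7.5% hypertonic saline in 6% dextran 70". Cellular and Molecular Biomarkers lists serum sodium, chloride and osmolarity among the measurements on hospital arrival and at 12, 24 and 48 hours.

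**The concern.** Sodium and its accompanying anions make up most of serum osmolarity, and HSD delivers sodium and chloride in equal moles. Limits for the three quantities should therefore be broadly compatible. Here the normal osmolarity band looks too high for the normal sodium band, and the upper chloride limits look too high for the upper sodium limits.

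These limits decide what is labelled normal, expected or unexpected for a primary feasibility endpoint that is meant to inform a definitive trial. If two of the three rows are set so that a salt effect registers late or is called normal, a low count in them reflects where the limits sit. It says little about the product.

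**Working it through.** **Inputs from Table 1** (assumed units mmol/L and mOsm/L)

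| | Normal | Expected up to | Unexpected |
|---|---|---|---|
| Sodium | 135-147 | 158 | >160 |
| Osmolarity | 310-330 | 350 | >350 |
| Chloride | 96-108 | 145 | >150 |

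**Assumption for osmolarity.** Osmolarity = 2 x Na + x, where x stands for glucose plus urea. The article gives neither the formula nor x, so x is varied.

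**Step 1. Can the printed normal osmolarity be reproduced from normal sodium?**

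| x | Na 135-147 implies | Osmolarity at Na 158 | Na at which 350 is reached |
|---|---|---|---|
| 5 | 275-299 | 321 | 172.5 |
| 10 | 280-304 | 326 | 170 |
| 15 | 285-309 | 331 | 167.5 |
| 20 | 290-314 | 336 | 165 |

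It cannot for x from 5 to 15. At x = 20 there is a marginal overlap (310 to 314). To reach 310 at all, x must be 310 - 2 x 147 = 16 at the top of normal sodium and 310 - 2 x 135 = 40 at the bottom. A variant formula, 1.86 x Na + x + 9, gives lower values still (270.1 to 292.4 at x = 10).

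**Step 2. Which sodium does the printed normal band describe?** At x = 10, (310 - 10)/2 = 150 and (330 - 10)/2 = 160. The band runs from above normal sodium to the sodium row's unexpected limit. It sits 310 - 280 = 30 above the implied range at the lower end and 330 - 304 = 26 above at the upper end. The step from normal to expected is consistent with sodium: 350 - 330 = 20, against 2 x (158 - 147) = 22. That pattern suggests a displaced row more than a deliberately wide one.

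**Step 3. When is the unexpected osmolarity limit reached?** At sodium 165 to 172.5 (Step 1, x from 20 down to 5), which is 5 to 12.5 above the sodium row's limit. It is exceeded with sodium at or below 160 only if x is more than 350 - 2 x 160 = 30.

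**Step 4. Chloride, from Table 1 alone.** Sodium minus chloride:

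- lower end of normal: 135 - 96 = 39
- upper end of normal: 147 - 108 = 39
- expected ceilings: 158 - 145 = 13
- unexpected limits: 160 - 150 = 10

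Chloride above 150 with sodium at or below 160 needs a difference of less than 10. At a difference of 20, chloride 150 corresponds to sodium 170; at 25, to 175; at 39, to 189.

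**Step 5. Chloride under an equal-mole salt load.** Equal moles do not mean equal rises in concentration, so a simple fluid balance is used. Assumptions: total body water 42 L, extracellular fluid 14 L, x = 10 at the start. One dose is 250 ml x 7.5% = 18.75 g; 18.75/58.44 = 0.321 mol, or 321 mmol of NaCl. For a salt amount m (mmol) in volume V (L) and starting osmolarity O0:

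- new osmolarity O = (42 x O0 + 2m)/(42 + V)
- new extracellular volume E = (14 x O0 + 2m)/O
- new sodium = (14 x Na0 + m)/E, and likewise for chloride

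One dose from mid-normal (Na 141, Cl 102, O0 = 292) gives sodium 148.2, chloride 112.9 and osmolarity 305.5. That patient is in the expected band for sodium and chloride but below the table's lower limit of normal for osmolarity. From the top of normal (147, 108), one dose gives 154.2, 118.8 and 317.4: expected, expected, and normal.

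Increasing m further, only to trace the path of a salt-driven rise:

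| Start Na/Cl | Cl when Na is 160 | Na when Cl is 150 |
|---|---|---|
| 135/96 | 131.2 | 175.4 |
| 141/102 | 129.2 | 176.5 |
| 147/108 | 127.0 | 177.8 |
| 135/108 | 140.0 | 168.5 |

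From the top of normal to sodium 160, sodium rises 13 and chloride 19, about 1.5 to 1. The table's expected ceilings allow 11 (147 to 158) and 37 (108 to 145), about 3.4 to 1.

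**The case against.** A reader might infer that neither row can record an event, so that both will report close to none whatever HSD does. The documents do not support this, for four reasons.

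- The osmolarity row excludes only alcohols. Other solute above about 30 (high glucose or urea, or another osmotic agent) would exceed 350 with sodium at or below 160. A very low sodium-chloride difference could likewise trip the chloride limit.
- Table 1 also has an expected column. Chloride above 108 falls in it, and a single dose from mid-normal takes chloride there. Only the upper chloride limits are in question; the normal range of 96 to 108 is not disputed.
- A salt-driven excess is still flagged by the sodium row at above 160, and the raw values of all three quantities are collected.
- One dose from mid-normal brings sodium only to about 148. Few unexpected events would be seen in the sodium row either, so low unexpected counts would not be due to the mismatch alone.

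It is also fair to say that the osmolarity formula is not in the article, that the literature behind the limits is not visible, and that separate analytes may have separate limits. Nothing requires all three rows to trigger at exactly equivalent levels.

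These points limit the consequence. They do not remove the inconsistency. The osmolarity mismatch persists for x from 5 to 15 and in the variant formula, and the fall in the sodium-chloride difference from 39 to 13 and 10 needs no formula.

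**Conclusion.** The point holds in limited form. The normal osmolarity band lies about 26 to 30 above what the table's sodium range implies at x = 10, so a patient with sodium of 150 to 160 is labelled as having normal osmolarity. For a salt-driven rise, the unexpected osmolarity limit is reached at sodium of about 165 to 172.5. The unexpected chloride limit is reached at about 175 to 178 from matched starting values, or 168.5 from the least favourable start tried. Both lie past the sodium row's own limit of 160.

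It does not follow that HSD effects go unrecorded. What is weakened is the osmolarity classification and the unexpected category for osmolarity and chloride, in rows labelled non serious. Normal osmolarity readings and low unexpected counts in these rows should not be taken as evidence of safety for the fourth feasibility endpoint.

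The osmolarity result rests on 2 x Na + x with x of 5 to 20. The chloride sodium-equivalents rest on the assumed fluid volumes, but the chloride differences come straight from Table 1. The units are assumed throughout.

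**What to change.** Before any adverse event rate is reported, the Steering Committee should, blinded to assignment:

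1. Reconcile the normal osmolarity range, and the expected and unexpected limits for osmolarity and chloride, with the sodium row and with the reference interval of the laboratory that measures them.
2. Print units in Table 1.
3. Classify the collected sodium, chloride and osmolarity values against the corrected table.

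No specific threshold is proposed here; the rows must be reconciled by those responsible for them. The chloride normal range can stay.

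The cost is a table correction and a classification run on values that the trial collects anyway. The downside is that some values now called normal or expected may count as events, so the reported rate may look less favourable.

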### Data Management

Paramedics complete a data checklist (Additional File 10) and standardized provincial patient care record. A single paramedic data abstractor will abstract data from the paramedic checklist and patient care record onto a prehospital case report form (Additional File 11). Site specific inhospital research staff will abstract data from the patient's chart daily and completed an inhospital case report form (Additional File 13). In-hospital patient data includes the interpretation of head CT scans employing the Marshall Classification system [50] as well as the Injury Severity Score [51]. Measures of organ dysfunction: Acute Physiologic and Chronic Health Evaluation (APACHE II)[52,53], Sequential Organ Failure Assessment (SOFA) [54] and Multiple Organ Dysfunction Score (MODS)[55] will be evaluated at ICU admission. In addition, SOFA and MODS will be recorded every other day until ICU discharge. Data entry onto a web based (prehospital data) or SAS version 8.0 interface (inhospital and follow up data) will be performed by a single trained data entry specialist.

### Analysis Plan

This is a feasibility study of two year's duration with a projected screening of 130 patients and recruitment of 100. The primary outcome measure, change in the proportion surviving 30 days post trauma between the treatment and control groups, will be analyzed by means of a generalized linear mixed model which included covariates of interest. The two groups are not expected to be different at baseline, and it is hypothesized that the treatment group would show a 20% decrease in mortality at 30 days post trauma whereas the control group would remain unchanged. To derive a reduced subset of risk factors for the predictor models, acceptable model building strategies are planned (i.e. dropping variables showing extremely small variability and those found to be highly correlated (i.e. correlation coefficient ≥0.8)). Treatment and time factors will be analyzed using a generalized linear mixed models of the secondary outcome repeated measures: the change in mortality after discharge over time as well as the neurocognitive and neuropsychological outcome summary scores. For secondary outcome analyses, the alpha will be adjusted to account for multiple comparisons. Where there is more than one measure for a neuropsychological test (e.g., processing speed, working memory, visuospatial, language, verbal memory, non-verbal memory - with the exception of executive processes, since different measures relate to different brain regions), a composite or prototypical measure will be derived from group comparison. Serial changes in all secondary immune modulation measures, neuro-biomarkers, neurocognitive and neuropsychological outcomes, and structural imaging measures will be evaluated by two-way ANOVA for repeated measures. All analysis will be conducted blinded to treatment assignment.

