### Intervention Protocol

All patients will be treated according to research medical directives (Additional File 2) based on a standardized provincial out of hospital trauma treatment protocol [6]. The study solution is started within 4 hours of the time the emergency call was received at ambulance dispatch. Samples of peripheral blood will be collected upon emergency department (ED) arrival, 12, 24 and 48 hours after ED arrival from a vein remote from the venous access site for the study infusion. Blood samples will be collected in heparinized and non-additive vacutainers by a single trained lab technician and immediately (within 1-h) shipped to a single designated laboratory for whole blood flow cytometric cellular analyses and measurement of circulating molecular immuno-inflammatory markers. Serum will be frozen for subsequent analyses. Whole blood will be incubated with saturating concentrations of the adhesion (CD62L-FITC, CD11b-PE), degranulation (CD66b-FITC, CD63-PE), apoptotic/necrotic (Annexin V-PE, 7-AAD, Active Caspase-3, CD95-Fas, CD178-FasL) markers, in conjunction with CD14-APC surface staining (to differentiate leukocyte subsets). Results will be acquired on a Becton Dickinson dual-laser (488 nm and 635 nm) BD FACSCalibur flow cytometer using CellQuest software. Serum samples will be analyzed for pro-/anti-inflammatory cytokines (TNF-α, IL-10), soluble leukocyte and endothelial-derived adhesion molecules (sICAM-1, sVCAM-1, sE-selectin, sL-selectin), pro-/anti-apoptotic molecules (sCD95, sCD95L, TNF-RI, sFas/FasL) and neuro-biomarkers of brain injury (S100B, NSE, MBP) (Additional File 3).

Magnetic Resonance Imaging on a 1.5 Tesla General Electric Signa Magnet is planned for completion at 4 months for consenting patients using a standardized protocol (Additional File 4, 5, 6, 7); a 3D 1.3 mm thick, T1-weighted, series (TE 4-2, TR 35, flip angle 35), an interleaved 3 mm thick PD and T2-weighted spin echo sequence (TE 39/80, TR 3000, flip angle 90) (Additional File 6), a gradient echo sequence and Diffusion Tensor Imaging (11 directions) (Additional File 7); tissue segmentation and parcellation including lesion quantification [7-12] using previously published in-house software as well as ANALYZE software [7,13].

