### Cellular and Molecular Biomarkers

Whole blood and circulating immuno-inflammatory markers will be measured on hospital arrival and at 12, 24 and 48 hours later

• Total leukocyte count and differential; neutrophil and monocyte surface expression of cellular adhesion molecules and degranulation markers: L-selectin (CD62L) and β_2_-integrin (CD11b) [36]

• Leukocyte apoptotic/necrotic surface and intracellular markers (Annexin V-PE, 7-AAD, Active Caspase-3, Fas (CD95), FasL (CD178) [37-42]

• Soluble pro-/anti-apoptotic molecules (sCD95, sCD95L, TNF-RI, sFas/FasL)[43]

• Leukocyte and endothelial-derived serum soluble adhesion molecule concentrations: intercellular adhesion molecule-1 (sICAM-1), vascular adhesion molecule-1 (sVCAM-1), sE-selectin, sL-selectin [44-46]

• Pro and anti-inflammatory cytokine expression: tumour necrosis factor (TNF)-α, and interleukin (IL)-10 [37,47,48];

• PT/PTT, tissue factor (TF), thrombomodulin (TM), fibrinogen, platelet count and Hg; Ionized calcium, and pH [49]

• Serum sodium, chloride and osmolarity

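### The two filters stated for the predictor models do not control overfitting in about 100 patients; its size depends on a candidate list and death count that the article does not give

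*Protocol article*

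**What the plan says.** The Protocol article, Study Objective, includes among the secondary objectives "evaluating the role of serum neuro-biomarkers in predicting patient outcome and clinical response to HSD intervention". Intervention Protocol names three such markers: "neuro-biomarkers of brain injury (S100B, NSE, MBP". They are measured in serum drawn at emergency department arrival and 12, 24 and 48 hours later. Cellular and Molecular Biomarkers gives the same schedule for a much longer list: "Whole blood and circulating immuno-inflammatory markers will be measured on hospital arrival and at 12, 24 and 48 hours later".

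For model building, the Analysis Plan spells out its strategies as "dropping variables showing extremely small variability and those found to be highly correlated", the limit being a correlation of at least 0.8. The filters are introduced with i.e., while the same paragraph uses e.g. for an open list of examples, so the two filters read as the whole rule. The planned size is a "projected screening of 130 patients and recruitment of 100". The article does not say which variables are candidates for the predictor models or how many deaths are expected.

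**The concern.** Dropping near-constant variables and one of each highly correlated pair is ordinary housekeeping. Both filters ignore the outcome. Neither ties the number of terms to the number of deaths, shrinks coefficients or corrects performance for being measured in the patients used for fitting. If all variables that pass go into a model on about 100 patients, apparent accuracy rises with the number of terms even when no marker carries information.

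The later samples add a second difficulty. They exist only for patients still alive and in hospital. The Discussion expects some patients to die in the emergency department and others to be discharged within hours. A model that uses all four samples is therefore fitted to a selected group.

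At stake is the biomarker-prediction objective: a reader could take chance fit for evidence that the markers predict outcome.

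**Working it through.** The plan has no figure for this to reproduce. It gives no number of candidates or deaths, and the 100 patients come without a power calculation.

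**Inputs**
- Patients: 100 (Analysis Plan).
- Deaths: not stated. Survival is something the study sets out to estimate ("baseline survival rates for the treatment and control group to aid in the design of a definitive multicentre trial"). Assumed: 20, 30, 40 or 50 deaths.
- Narrow candidate set: 3 neuro-biomarkers at arrival, or 3 × 4 = 12 over four samples.
- Broad candidate set, counted from Intervention Protocol, Structural Outcomes and Cellular and Molecular Biomarkers: leukocyte count and differential 2, adhesion 2, degranulation 2, cell apoptosis/necrosis 5, soluble apoptotic 4, soluble adhesion 4, cytokines 2, coagulation and related 9, sodium/chloride/osmolarity 3, neuro-biomarkers 3, C-reactive protein 1. The sum is 37 at one time, and 37 × 4 = 148 over four. The count shifts a little with how overlapping markers and cell subsets are treated.

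**Step 1. Deaths per candidate** (deaths ÷ candidates, for 20 and 50 deaths)
- 3 candidates: 20/3 = 6.7 to 50/3 = 16.7
- 12 candidates: 20/12 = 1.7 to 50/12 = 4.2
- 37 candidates: 20/37 = 0.5 to 50/37 = 1.4
- 148 candidates: 20/148 = 0.14 to 50/148 = 0.34

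**Step 2. What the 0.8 filter removes.** It removed none of a set of independent noise variables. Of 148 serial measures it kept 148 when the correlation between repeat samples of one marker was 0.5, about 146 at 0.7, about 83 at 0.8 and 37 at 0.9.

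**Step 3. Apparent accuracy of noise.** In each simulated trial, 100 patients had the fixed number of deaths and p standard normal predictors unrelated to death. The 0.8 filter was applied and every remaining variable entered a logistic model. Apparent AUC is the share of death–survivor pairs in which the death has the higher fitted score. Means over 200 runs (400 for p = 12):

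| Candidates p | 20 deaths | 30 deaths | 40 deaths | 50 deaths |
|---|---|---|---|---|
| 3 | 0.62 | 0.60 | 0.59 | 0.59 |
| 5 | 0.65 | 0.63 | 0.62 | 0.62 |
| 12 | 0.74 | 0.71 | 0.70 | 0.70 |
| 20 | 0.82 | 0.78 | 0.76 | 0.75 |
| 37 | 0.96 | 0.90 | 0.88 | 0.87 |

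In new patients the same models had an AUC of about 0.50 throughout. Repeat runs gave 0.69–0.75 for 12 candidates and 0.87–0.97 for 37. With all 148 serial measures (30 deaths, 40 runs), fitting was perfect (AUC 1.00) at repeat-sample correlations up to 0.8. At 0.9 it was 0.90.

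**Step 4. Predicting response to HSD.** This ordinarily needs marker-by-treatment terms: 12 + 1 + 12 = 25. Mean apparent AUC of noise was then 0.86, 0.82, 0.80 and 0.79 for 20, 30, 40 and 50 deaths.

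**Step 5. Outcomes other than death.** For a continuous outcome and a linear model, the expected R² of p noise predictors in n patients is p/(n − 1). With n = 100 this is 3/99 = 0.03, 12/99 = 0.12 and 37/99 = 0.37. Fewer patients would reach the 4-month scales, so these values are lower bounds.

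**The case against.** The strongest reply is that the candidate set is unknown. The objective names only serum neuro-biomarkers, so 12 candidates may be the most that enter. The Analysis Plan sends the immune measures to repeated-measures ANOVA, and nothing places some 37 analytes in a prediction model. The filter sentence also follows the primary survival model with its covariates, so it may concern covariate reduction there. Finally, a condensed article may leave shrinkage and validation to a fuller plan.

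Much of this stands. A reader might infer that the filter leaves far more candidates than deaths. The article does not support that: it gives neither number, and the statement holds only if every measure at every time is a candidate. At one time point 37 candidates are of the same order as 20 to 50 deaths, and 12 are fewer. A reader might also infer that a false biomarker signal would pass into the definitive trial. What the article says will inform that trial's design is the survival rates, and the Discussion treats the additional tests as exploratory. Absence of shrinkage or validation from this article is not proof that none is planned.

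The reply does not rescue the rule. The text refers to predictor models in the plural and states how their variables will be reduced, and that rule gives no protection even with 12 candidates. The alpha adjustment for secondary outcomes and the blinded analysis address other problems.

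**Conclusion.** The point holds in conditional form. The stated rule does not control overfitting in about 100 patients. With pure noise and 20 to 50 deaths, the mean apparent AUC is about 0.6 for three arrival markers, about 0.70–0.75 for 12 candidates and about 0.87–0.97 for 37, against a true 0.50.

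These figures rest on four assumptions: the death count, a complete sample of 100, entry of every variable that passes the filters, and no real signal. The last is imposed to measure optimism; it is not a claim that the markers are uninformative. AUC is used as a convenient scale, since the article does not name its performance measure. Consent for blood analysis and early deaths or discharges would probably reduce the usable sample and worsen the optimism.

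The objective is secondary, so the point is minor to moderate.

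**What to change.** For the biomarker-prediction objective, state in the Analysis Plan:

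- The candidates are S100B, NSE and MBP from the arrival sample, plus a few baseline covariates already collected, fixed before the data are seen. The two filters may stay as data checks, but not as the means of controlling model size.
- Performance is reported after bootstrap correction for optimism, with the whole model-building process repeated in each bootstrap sample. This is needed even for a small model, because five noise candidates still give an apparent AUC of 0.62–0.65. If more terms are entered, including marker-by-treatment terms, a penalised fit is used. The type of penalty and the exact covariates are for the trial team to choose.
- A marker from the 12-, 24- or 48-hour sample is used only to predict outcomes after that time, among patients then alive and sampled, with their number reported.
- Models using any other markers are labelled exploratory.

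It should also say whether the filter sentence governs the covariates of the primary survival model. The cost is analysis wording, some programming and a lower reported predictive accuracy. No extra patients, samples or visits are needed.
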